### 3 Hypotheses and Success Metrics

The primary hypotheses that will be tested in this study as well as the endpoint indicators for success are listed in Tables 2 and 3 below and are based on three primary outcomes: coverage, reduction in malnutrition, and reduction in clinical malaria.

Table 2: Research Hypotheses

| #   | Hypotheses                                                                                                                                                |
|-----|-----------------------------------------------------------------------------------------------------------------------------------------------------------|
| H-1 | Coverage and adherence of SMC among eligible children in areas where SMC + LNS was delivered will not differ from areas where only SMC was delivered.     |
| H-2 | Nutrition indicators among eligible children in areas where SMC + LNS was delivered will not differ from areas where only SMC was delivered.              |
| H-3 | The odds of being diagnosed with clinical malaria cases including severe cases among eligible children who received SMC + LNS, SMC, or neither treatment. |

Table 3: Performance Metrics

| Hypotheses | Performance Indicator | Indicator Definition and Unit of Measurement                                                                                                                                                                                                                                                                                                                                                                                                                    | Data Source                                    |
|------------|-----------------------|-----------------------------------------------------------------------------------------------------------------------------------------------------------------------------------------------------------------------------------------------------------------------------------------------------------------------------------------------------------------------------------------------------------------------------------------------------------------|------------------------------------------------|
| H-1        | Monthly Coverage      | 
Monthly Coverage
 
Indicator Definition: Percent of children 6-24 months* who received a dose of treatment^ out of the total number of eligible children surveyed during each administration period (July, August, Sept, and October).
 
Unit of Measurement: Percentage
 
* The age class will evolve and not always be 6-24 months.
 
^ Treatment refers to the intervention (either LNS + SMC or SMC alone).
 | Midline household survey                       |
| H-1        | Adherence             | 
Adherence
 
Indicator Definition: Percent of children 6-24 months who completed the three-day treatment course of SMC out of the total number of children who received SMC during the final round of intervention administration.
 
Unit of Measurement: Percentage
 
* The age class will evolve and not always be 6-24 months.
                                                                                     | Midline Household survey                       |
| H-2        | Malnutrition          | 
Stunting (Height for Age)
 
Indicator Definition: Percent of children 6-24 months* whose height is more than 2 standard deviations below the median for the international reference population age 6-24 months. For children under 2 years recumbent length will be used.
 
Unit of Measurement: Percentage
 
* The age class will evolve and not always be 6-24 months.
                                             | Household surveys (baseline, midline, endline) |
| H-2        |                       | 
Wasting (Weight for Height)
 
Indicator Definition: Percent of children 6-24 months* whose weight for height is more than 2 standard
                                                                                                                                                                                                                                                                                                  | Household surveys (baseline, midline, endline) |

|     |                  |                                                                                                                                                                                                                                                                                                                                                                                                   |                                                   |
|-----|------------------|---------------------------------------------------------------------------------------------------------------------------------------------------------------------------------------------------------------------------------------------------------------------------------------------------------------------------------------------------------------------------------------------------|---------------------------------------------------|
|     |                  | 
deviations below the median for the international reference population age 6-24 months. For children under 2 years recumbent length will be used.
 
Unit of Measurement: Percentage
 
* The age class will evolve and not always be 6-24 months.
                                                                                                                          |                                                   |
| H-2 |                  | 
(Underweight) (Weight for Age)
 
Indicator Definition: Percent of children 6-24 months* whose weight for age is more than 2 standard deviations below the median for the international reference population age 6-24 months.
 
Unit of Measurement: Percentage
 
* The age class will evolve and not always be 6-24 months.
                            | Household surveys
(baseline, midline, endline) |
| H-3 | Clinical Malaria | 
Clinical Malaria
 
Indicator Definition: Number of clinical confirmed malaria cases among children 6-24 months per 1,000 children 6-24 months in the estimated catchment areas of the facilities)
 
Unit of Measurement: Odds-Ratio among cases and controls, and incidence
 
* The age class will evolve and not always be 6-24 months.
               | Malaria case tracker(Case-Control study)          |
|     |                  | 
Severe Malaria
 
Indicator Definition: Number of hospital admissions for confirmed severe malaria among children 6-24 months per 1,000 children 6-24 months in the estimated catchment areas of the facilities)
 
Unit of Measurement: Odds-Ratio among cases and controls, and incidence
 
* The age class will evolve and not always be 6-24 months.
 | Malaria case tracker
(Case-Control study)      |

## 4 Intervention Design

### Study Site and Population

Table 4: Overview of the study population for each treatment type.

| Intervention Arm                                               | LGA    |
|----------------------------------------------------------------|--------|
| Arm 1: SMC (Children 3-59 months)                              | Madobi |
| Arm 2: SMC (Children 3-59 months) + LNS (Children 6-24 months) | Madobi |

This study has two intervention arms: SMC delivery and SMC + LNS delivery. Of note, SMC is specified by the WHO for children 3-59 months and Plumpy'doz' is specified by UNICEF and WFP for children 6-24 months, this study will treat children in intervention arms based on these recommendations (see Table 4: Intervention Arm). In the Local Government Area (LGA), Madobi, between 1 and 3 wards were selected for each intervention arm. An overview of the study population for each intervention area is presented in Table 4. The intervention areas were chosen to be as similar as possible in terms of pre-determined criteria that included malaria incidence reported at public health centers, wasting prevalence, malaria endemicity, socio-economic status, urbanicity, mobility and cultural identity of the population, density of health facilities, presence of a CMAM facility, and population demographic structures (dependency ratio, fertility rate and household size, infant mortality, and birth spacing).

### Overview of the Intervention Arms

Roll-out of the intervention will consist of two phases which are detailed below.

#### Phase 1: Community Sensitization

Sensitization to the intervention (either SMC or SMC + LNS) and the delivery method (door-to-door distribution) for each intervention arm area will take place on the community level using the pre-existing political structure and social network groups. Sensitization and mobilization will start at the state level with high-level advocacy meetings with key directorate heads in the KSMOH, head of hospitals management board, primary health care management board, and development partners. The SMC technical working group inaugurated in 2013 will gather to discuss progress, identify challenges, and

 WHO Global Malaria Programme (March 2012). WHO Policy Recommendation: Seasonal Malaria Chemoprevention (SMC) for *Plasmodium falciparum* malaria control in highly seasonal transmission areas of the Sahel sub-region in Africa.

develop mitigation strategies. Community level mobilization will then commence four weeks to the start of proposed administration period. In each community CHAI will support the KSMCP to host LGA and ward level meetings. Meetings will take place at the LGA secretariat or district/ward head's house and will bring together staff of the LGA Health Department and Health Education Unit as well as District, Ward, and village heads, religious leaders, and heads of health facilities. Participants will be sensitized to the treatments, benefits and risks, eligibility requirements, intervention timing, and procedures. Poster and fliers that have been created by the Behavioural Change Campaign (BCC)/Advocacy Unit of the KSMOH will be presented and then distributed to key stakeholders to be posted in health facilities and strategic places within their communities and for distribution within the community. Immediately after the meeting, village leaders will be supported to commence sensitization in their respective villages and ensure community uptake. One week prior to each administration period, ward, village, and health facility heads and religious leaders will announce intervention delivery details on a continuous basis to their catchment populations to reinforce the message. Additionally, town criers will be engaged to disseminate the message of treatment delivery. Of note, all parents/guardians will be requested to provide the drinking water for their child to ingest the drugs.

### **Phase 2: Intervention Administration**

Phase 2 will make use of the existing network of Community Drug Dispensers (CDDs) that work on other health campaigns in Kano. Community lists will be obtained for each ward from the Village head or the CDD LGA Focal person. Within each ward, CHAI study staff will visit each identified community and a household sampling frame will be obtained from each community headman. In the event that a Village head cannot produce an accurate listing or new communities have developed that are not present on the village head's list, the village headman and CDDs will be used to create a census of their community. CDDs alongside study staff will visit each household on the sampling frame and obtain accurate listings of homes with at least one child under-five residing within it in the treatment area. Supplementary data will also be collected from parents/guardians including data on the number of children 3-59 months of age residing in each home, child and parent's/guardian's names, and contact details (e.g. phone number of parent/guardian, address of home).

CHAI will train pre-existing CDDs on the proper administration of SP-AQ/*Plumpy doz'* in a 1-day training course. During each administration period, each CDD will be assigned to 100 households that they will cover over the course of one week. The CDDs will visit children and their parents/guardians in their homes four times on a monthly basis (July-October) and deliver the treatment. After each visit, CDDs will instruct parents/guardians that they will return four weeks later, on the *same day of the week* as the first SMC visit to deliver the next treatment.

All treatments provided will be recorded in two places: a treatment card that is left with the parent/guardian of the child and the CDDs administration register. Each child will be assigned a unique Identification number (ID) and the treatment card and the child's name in the CDDs administration register will be labeled with the unique ID. The treatment card will be filled out by the CDD at first contact, and given to the parent/guardian of each child. Information collected on the treatment card will include the child's name, birthday, dose of SP-AQ and amount of LNS provided, date of

administration, and date of next visit. In addition to the information included on the treatment card, the CDD's administration register will also include the child's sex, parent's/guardian's name and the village's name and compound's address where the child resides. Children that meet the inclusion criteria in terms of age but do not meet all the inclusion criteria listed on pages 11-14 will be given a treatment card with a reference indicating why they were excluded from treatment this round. Each child's identity will be checked before treatment is given and no treatment will be provided without the parent's/guardian's written consent.

## **SP-AQ Administration**

### **Dosing Procedures**

The KSMOH and the KSMCP provided administration clearance for mass drug administration, dosing, and the study procedures. Dosing guidelines for SP-AQ are presented in Table 5 below and follow the WHO guidelines for SP-AQ delivery. SP-AQ will be provided once per month, ideally on the same day each month, for 4 consecutive months during the long rainy season (July 15 – October 15). A person trained in SP-AQ administration and the signs and symptoms of adverse reactions will administer the SP-AQ. Following drug ingestion, children will remain under observation for 15 minutes. In the event of spit-up or vomiting drugs will be re-administered alongside food, water, or breast milk. The first dose of SP-AQ, consisting of both SP and AQ tablets, will be administered through directly observed therapy (DOT) whereby children are observed taking the drug by the health worker or parent /guardian administering the drug. Parents/guardians will then be given the remainder of the co-blister (containing two AQ tablets each given on the respective two days) and instructions on how to administer the drug on days 2 and 3. In young children unable to swallow the SP-AQ, the CDD will recommend that the SP-AQ tablets be crushed and mixed with water and sugar. The CDD will provide sugar for the full three days of treatment.

### **Inclusion/Exclusion Criteria**

All children 3-59 months at the first round of administration (July), residing in either intervention areas, and do not meet one of the exclusion criteria listed below are eligible to receive SMC. The child's parent/guardian must also sign an informed consent either with their signature or right thumbprint prior to administration.

Of note, if a child ages out during the study (is eligible at administration round 1 in July and subsequently turns 60 months prior to administration round 2, 3, or 4), he/she will remain enrolled in the intervention and continue to be eligible for SMC provided he/she does not meet the exclusion criteria below.

#### **Exclusion Criteria:**

- A child is 0-3 months of age or above 59 months of age.
- A child with severe acute illness or unable to take oral medication
- A child that has confirmed or suspected malaria. Confirmed malaria is defined as fever (body temperature  $\geq 37.5^{\circ}\text{C}$ ) or history of fever in the last 24 hours and parasitologically positive by Rapid Diagnostic Test (RDT) or microscopy; in the

absence of RDT and microscopy diagnosis, malaria diagnosis should be based on clinical signs and symptoms.

- An HIV-positive child and receiving co-trimoxazole.
- A child who has received a dose of either AQ or SP drug more recently than the past month.
- A child who is allergic to either drug (AQ or SP).

Children with severe acute illness or high fever that are not currently under a clinician's care will be referred to the nearest public health facility.

Table 5: Dosing guidelines for eligible children.

| Product and Dosing Information for SPAQ-CO |                                                                                                                                                                                                                                   |                          |                   |              |                   |              |                   |
|--------------------------------------------|-----------------------------------------------------------------------------------------------------------------------------------------------------------------------------------------------------------------------------------|--------------------------|-------------------|--------------|-------------------|--------------|-------------------|
|                                            | 
Brand Name and Formulation: SPAQ-CO
 
Co-blister of Sulfadoxine/pyrimethamine tablets + Amodiaquine tablets (SP+AQ)
 
Vendor: Guilin Pharmaceuticals
 
Catalog ID: 3.2.05.28.001.01.02
 |                          |                   |              |                   |              |                   |
|                                            |                                                                                                                                                                                                                                   | Day 1             |                   | Day 2 |                   | Day 3 |                   |
| Product Name and Formulation               | Age range                                                                                                                                                                                                                         | SP*                      | AQ*               | SP*          | AQ*               | SP*          | AQ*               |
| Infant Dose – AQ75mg + SP262.5mg           | 3 months to <12 months                                                                                                                                                                                                            | 1 tablet (250mg /12.5mg) | 1 tablet (75 mg)  | Nil          | 1 tablet (75mg)   | Nil          | 1 tablet (75 mg)  |
| Child dose – AQ150mg + SP525mg             | 12 months to 59 months                                                                                                                                                                                                            | 1 tablet (500mg /25mg)   | 1 tablet (150 mg) | Nil          | 1 tablet (150 mg) | Nil          | 1 tablet (150 mg) |

\*SP: Sulfadoxine/Pyrimethamine tablets; AQ: Amodiaquine tablets

 Guilin Pharmaceutical Co., Ltd.

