## Plumpy'Doz' Administration

### Dosing Procedures

For children in the SMC + LNS intervention arm, LNS will be provided to eligible children 6 to 24 months of age and is intended for daily use during the four-month intervention period. The monthly ration of LNS will be provided to the primary caregiver by the CDD at the same time of SP-AQ distribution. The first serving of LNS will be provided alongside the first dose of SP-AQ under DOT. The product does not require any preparation, and should not be cooked or diluted. Caregivers will be instructed that LNS should be given in addition to breast milk and other available foods. The LNS will not be provided to children less than 6 months of age, so as not to interfere with exclusive breastfeeding. Following the first dose, parents/guardians will be instructed to continue to serve eligible children LNS daily following the serving guidelines in Table 6. The recommended daily dose of Plumpy'DozTM is 1.5 teaspoons (6-11 months of age) or 3 teaspoons (12-23 months of age), served 3 times per day; this is a total of 23 grams per day for children 6-11 months of age and 46 grams per day for children 12-23 months of age. One container of 325 grams is intended to serve one child for one week and each child will receive 4 containers for the entire month alongside the monthly SP-AQ treatment course. The pot will need to be resealed and stored in hygienic conditions between servings.

Table 6. Recommended Daily and Monthly Dosing of Plumpy'Doz

| Age (months) | Recommended Plumpy'Doz Servings, per Day | Kilocalories, per Day | Number of Servings, per Day | Recommended Plumpy'Doz Servings, per Month |
|--------------|------------------------------------------|-----------------------|-----------------------------|--------------------------------------------|
| 6-11         | 23 grams                                 | 123 kcal              | 3 servings                  | 690 grams                                  |
| 12-23        | 46 grams                                 | 147 kcal              | 3 servings                  | 1,380 grams                                |

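### Two field rules do not fit the protocol's own schedule and doses: the AQ/SP washout does not exempt the campaign's previous course, and the LNS ration ignores the age-specific dose

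*Protocol*

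**What the plan says.** **SP-AQ washout.** The Exclusion Criteria for SP-AQ list "A child who has received a dose of either AQ or SP drug more recently than the past month". No exemption is written for a course given by the campaign itself. Two places show that exclusion is judged in later rounds:

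- Phase 2: Intervention Administration says that children of eligible age who fail another criterion "will be given a treatment card with a reference indicating why they were excluded from treatment this round".
- The Inclusion/Exclusion Criteria say of a child who turns 60 months during the study that "he/she will remain enrolled in the intervention and continue to be eligible for SMC provided he/she does not meet the exclusion criteria below".

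**Round interval.** Phase 2 says that after each visit "CDDs will instruct parents/guardians that they will return four weeks later", and the same section calls the visits monthly. The SP-AQ Dosing Procedures say "SP-AQ will be provided once per month, ideally on the same day each month, for 4 consecutive months during the long rainy season", with 15 July to 15 October as the season. The first dose is observed; caregivers then get the remaining AQ tablets with "instructions on how to administer the drug on days 2 and 3". Table 5 confirms AQ alone on those two days.

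**LNS ration.** The Plumpy'Doz Dosing Procedures set 23 g a day at 6-11 months and 46 g a day at 12-23 months. They also say "One container of 325 grams is intended to serve one child for one week and each child will receive 4 containers for the entire month", with no split by age. Table 6 gives monthly amounts of 690 g and 1,380 g. The quantity instruction for caregivers is to follow the Table 6 servings.

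**The concern.** Both are rules that distributors apply at the door after one day of training, so the written text should say what is meant.

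The washout counts any dose of either drug, and the campaign gives both drugs about every four weeks. Applied as written, it can turn a child away because the previous round was taken. It also falls hardest on children who finished the course, since the later AQ tablets shorten the gap.

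The ration is the same for all ages while the dose doubles at 12 months. One of the two statements must be wrong for the younger children. At stake are surplus stock in households with a 6-11-month-old and an LNS supply figure that does not follow from the dose table.

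**Working it through.** **1. Age of the previous doses at the next visit**

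For a round interval of I days, the day 1, 2 and 3 doses are I, I − 1 and I − 2 days old.

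- Four-week return, I = 28: 28, 27 and 26 days.
- 15 July, 15 August, 15 September, 15 October (my reading of the same-day-each-month wording): I = 31, 31, 30. The day-3 AQ dose is then 29, 29 and 28 days old.

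The protocol does not define a month for the washout, so both definitions are shown:

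| Round interval | Doses counted | Month = 28 days | Calendar month (30-31 days) |
|---|---|---|---|
| 28 days | every dose | barred (27, 26) | barred |
| 28 days | day 1 only | just clears (28 against 28) | barred |
| 30-31 days | every dose | clears (28 or more) | barred (days 2 and 3) |
| 30-31 days | day 1 only | clears | just clears |

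The criterion names a dose of either drug, so counting every dose is the literal reading. At the four-week return that reading bars a child who completed the course under both definitions of a month.

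**2. LNS supply against need**

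Table 6 is reproduced with a 30-day month: 23 × 30 = 690 g and 46 × 30 = 1,380 g. The ration is 4 × 325 = 1,300 g.

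| | 6-11 months (23 g/day) | 12-23 months (46 g/day) |
|---|---|---|
| Need over 28 days | 23 × 28 = 644 g | 46 × 28 = 1,288 g |
| Ration / 28-day need | 1,300/644 = 2.02 | 1,300/1,288 = 1.01 |
| Ration / Table 6 | 1,300/690 = 1.88 | 1,300/1,380 = 0.94 |
| Ration − Table 6 | +610 g | −80 g |
| One container lasts | 325/23 = 14.1 days | 325/46 = 7.1 days |
| Four containers last | 1,300/23 = 56.5 days | 1,300/46 = 28.3 days |

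A container lasts a week only at the older children's dose. For a child who stays under 12 months through four 28-day rounds, supply is 4 × 1,300 = 5,200 g and need is 112 × 23 = 2,576 g. The surplus is 2,624 g, about 8.1 of 16 containers.

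**3. Clerical items nearby**

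- The LNS exclusion list gives 6-24 months as an exclusion, although the inclusion sentence above it gives that range as eligible.
- Table 6 implies 123/23 = 5.35 and 147/46 = 3.20 kcal per gram for one product. The protocol does not show which entry is wrong.

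**The case against.** On the washout, the intent is plain. The regimen is four courses, and distributors are sent back expressly to give the next one. The conflict depends on how an undefined month is counted: it disappears with a 28-day month counted from day 1, or with 30-31 day spacing and a 28-day month. The ageing-out clause shows that the list cannot be read literally throughout, because it keeps children who turn 60 months subject to a list that excludes those above 59 months. Nothing suggests that trained distributors would refuse the round they came to deliver. All of this stands and limits the point to wording. It does not supply the missing exemption: the protocol makes a later-round exception for age but none for the previous course.

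On LNS, the container statement describes supply. A reader might infer that infants are prescribed a double dose, or that caregivers receive two conflicting instructions. The protocol supports neither: it does not say caregivers are told that a pot lasts a week, and the serving guidelines they are given are age-specific. The 80 g gap at 12-23 months arises only because Table 6 uses 30 days. A uniform pack may also be a deliberate simplification, though no reason is given. What remains is that the ration contradicts the 6-11 month dose on any length of month.

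**Conclusion.** The point holds as two drafting inconsistencies in field rules, and it is minor.

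- **Washout:** read literally at the four-week interval, it excludes children who completed the previous course from rounds 2 to 4. This rests on counting every AQ or SP dose. It is clearly not intended.
- **Ration:** four containers are 1.88 to 2.02 times the 6-11 month need and fit the 12-23 month need over 28 days. This rests only on the protocol's own doses and container size.

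A reader might go further and infer that rounds 2 to 4 cannot be delivered, or that the comparison between arms is biased. The protocol does not support that. The SP-AQ rule is the same in both arms, and nothing indicates that it would be applied against the planned schedule. Sample size, alpha and power do not depend on either rule.

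**What to change.** **Washout.** Exempt the campaign's own previous course, or require at least 28 days from its day 1. State one round interval in Phase 2, the SP-AQ Dosing Procedures and the Exclusion Criteria.

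**Ration, four-week cycle.** Give two containers at 6-11 months (650 g against 644 g) and four from 12 months (1,300 g against 1,288 g), with the number set by the age reached before the next visit. Two containers leave only 6 g of slack, about a quarter of a day, so allow a third if visits may run late. Limit the one-container-a-week statement to the older group and put the Table 6 monthly amounts on the same 28 days.

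**Ration, 30-31 day cycle.** Two containers fall short by 690 − 650 = 40 g to 713 − 650 = 63 g, and four by 1,380 − 1,300 = 80 g to 1,426 − 1,300 = 126 g. Three (975 g) and five (1,625 g) would be needed.

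**Clerical.** Reword the LNS age exclusion to children below 6 months, or above 24 months at round 1, keeping the ageing-in and ageing-out provisions. Check the Table 6 energy column against the product label.

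**Cost.** Protocol wording and distributor training material. On a four-week cycle, each 6-11-month-old needs two fewer containers per round, or one fewer if a third is allowed. On a 30-31 day cycle, it is one fewer for that group and one more for each older child. There is no statistical cost.
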